### Trial assessment schedule

Children will be intensively monitored during admission by the clinical team at least eight hourly in the first 72 hours following recruitment, and daily thereafter. Locator maps and contact numbers will be obtained to facilitate follow-up. All participants will then be seen at seven-days, 28-days and 90-days post-admission at outpatient clinics attached to each centre for evaluation of morbidity and toxicity. Any patient not returning for a study visit will be traced for vital status ascertainment (
Table 2).

**Table 2. T2:** Schedule of clinical assessments and laboratory investigations.

Procedure	Rand *	0m	30m	60m	90m	2hr	4hr	8hr	24hr	48hr	Daily	Disc *
**Source documents**	X	X	X	X	X	X	X	X	X	X	X	X
Clinical notes (doctor) ^ $ ^	X	X	X	X	X	X	X	X	X	X	X	X
Bedside observations (nurse)	X	X	X	X	X	X	X	X	X	X	X	
Haemoglobin (Hb)	X							X	X	X		
Lactate	X							X	X			
Glucose	X					X		X	X			
Prescription chart	X								X	X	X	X
Anthropometry	X											X
Case report form	X	X	X	X	X	X	X	X	X	X		X
Diagnosis ^ ¢ ^	X											X
Drugs received									X	X		X
Transfusion and iv fluids charts			X	X		X	X	X	X	X		X
Locator details	X											X
Investigations ^ & ^	X					X		X	X	X	X	
Serious adverse events		X	X	X	X	X	X	X	X	X	X	X
Discharge medication												X

* Rand: At randomisation; Disc: On Discharge from hospital
^$^ Additional reviews by doctors and nurses will be conducted and recorded, where clinically indicated.
^&^ Laboratory tests and bedside tests including glucose and lactate at time points shown; plus any additional investigations as clinically required eg chest-Xray 
^¢ ^Working diagnosis at admission and final diagnosis at discharge.

### Blood sampling schedule

Following consent and randomisation, blood samples will be taken for the following investigations: full blood count, urea and electrolytes, lactate, glucose, malaria status (malaria slide), blood culture and other clinically indicated investigations (not required by the study protocol). Urine will be taken as soon as possible after trial enrolment for multi-stick analysis for assessment of cola or red colour urine and additional storage for later analysis of gut barrier function. In accordance with national guidelines, HIV testing will be performed during admission procedures since this is one of the eligibility criteria. Pre- and post-test counselling will be done in accordance with routine practice. At admission, a venous blood sample will be collected into Heparin and EDTA tubes and stored for subsequent cytokine and biomarker assays, parasitological (
*P. falciparum* HRP2), genetic studies (including sickle cell and glucose-6-phosphatase deficiency status) and immune activation studies (transcriptome and cellular assays). For the latter, red and white cell pellets will be prepared and stored. Further blood samples will be taken at 72 hours, seven days and 28 days (for biomarker assays and immune activation studies); and at day seven for repeat blood culture (see
Table 3). Changes in inflammatory markers (including CRP and procalitonin, PCT) will be measured retrospectively at 72 hours and day seven and microbiology cure measured at day seven (from blood cultures and using non-culture based molecular diagnostics on stored blood).

**Table 3. T3:** Detailed laboratory investigation schedule.

Day from recruitment	D0	D1	D3	D7	D28
Blood culture	3 ml			3 ml (cases)	
PK studies (cases only)	2 x 0.25 ml			1 x 0.25 ml	
Whole blood (Endotoxin)	1.5 ml		1.5 ml	1.5 ml	
Whole blood EDTA (genetics)	1 ml				
Whole blood (transcriptomics, CRP, procalcitonin, calprotectin, gut barrier function)	4.5 ml		2 ml	2 ml	4.5 ml
**Total blood volume research**	**10.4 ml**	**0.5 ml**	**3.5 ml**	**7 ml**	**5 ml**
Urine	x	x	x		

PK, pharmacokinetics; CRP, C-reactive protein.

### Clinical management and monitoring

All trial patients will receive standard of care including (intravenous or oral) anti-malarial drugs following national guidelines, based on WHO syndromic patient management
^
29
^. We will collect data on all administered drugs. Antipyretics, anticonvulsants and treatment for hypoglycaemia will be administered according to nationally agreed protocols. If required, maintenance fluids will be run at 3-4 ml/kg per hour irrespective of age until the child can drink and retain oral fluids. As the trial is designed to target the use of ‘appropriate’ antimicrobial treatments, clinicians will be free to prescribe antibiotics other than cephalosporins, quinolones or macrolides on admission day two based on the child’s clinical condition and according to country guidelines. On day three (or earlier if results available) clinicians will be permitted to prescribe broad-spectrum antimicrobials guided by the admission blood culture results (species and/or susceptibility). The Uganda severe malaria guidelines give no specific guidance on the use of antibiotics in severe malaria. Children or their carers will be provided with an appropriate supply of azithromycin drugs if discharged before day five.

The clinical coordinator is responsible for ensuring the discharge check-list is complete and for chasing up inpatient notes at discharge. Any relevant information, especially with regard to date of discharge, serious adverse events (SAEs), treatments, blood transfusions, use of intravenous fluids, oxygen or non-routine treatments or investigations, will be recorded. Children will be assessed on day seven, day 28 and day 90 following recruitment. The parent/guardian will receive a follow up invitation on a card. A symptom checklist and targeted physical examination will be performed at each clinic visit post-discharge. Medical history since last visit including hospital re-admissions, transfusions and grade three or four adverse events related to the antibiotic interventions including severity and likely relationship of any adverse events will be documented by a doctor. Any child lost to follow-up before 90 days will be traced for vital status. In order to minimise losses to follow-up, locator data (maps and identifiable landmark) and mobile phone numbers will be taken on discharge and verified at every review. During the 90 day study period attempts will be made to contact the patient via phone (if available) and to follow-up with home visits, if clinic visits are not attended. In the statistical analysis, a patient will be regarded as ‘lost to follow-up’ if they were not seen in clinic at the day 90 visit and were not known to have died.

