### Randomisation procedure

Randomisation lists will be generated and kept at the Medical Research Council (MRC) Clinical Trials Unit at University College London, London. The randomisation envelopes will be prepared before the trial, using the lists at the Clinical Trials Facilty, KEMRI Wellcome Trust Research Programme (KWTRP), Kilifi, Kenya. These will be opaque and sealed and will contain a card with allocation. Children will be randomised (1:1:1) to receive 10, 15 or 20 mg/kg azithromycin (based on weight-bands). The cards will be numbered consecutively and opened in numerical order. Clinicians will be aware of the treatment-group dose assignments, but the laboratory tests are to be performed in a blinded manner.

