### Pragmatic dosing chart

Rather than calculate azithromycin doses based on body weight (which in practice is poorly implemented), the trial will use weight bands (see
Table 1) all using 100mg dispersible tablets, which are more practical and generalizable outside of clinical trials.

**Table 1. T1:** Pragmatic dosing chart for dispersible azithromycin.

	10 mg/kg	100mg tabs	15 mg/kg	100mg tabs	20 mg/kg	100mg tabs
Weight (kg)	Weight x10	Tab size	Weight x15	Tab size	Weight x20	Tab size
5.5 - 6.4	55-64	0.5	82.5-97	1	110-129	1
6.5 - 7.4	65-74	0.5	97.5-112	1	130-149	1.5
7.5 - 8.4	75-84	0.5	112.5-127	1	150-169	1.5
8.5 - 9.4	85-94	1	127.5-142	1.5	170-189	1.5
9.5 - 10.4	95-104	1	142.5-157	1.5	190-209	2
10.5 - 11.4	105-114	1	157.5-172	1.5	210-229	2
11.5 - 12.4	115-124	1	172.5-187	1.5	230-249	2.5
12.5 - 13.4	125-134	1	187.5-202	2	250-269	2.5
13.5 - 14.4	135-144	1.5	202.5-217	2	270-289	2.5
14.5 - 15.4	145-154	1.5	217.5-232	2	290-309	3
15.5 -16.4	155-164	1.5	232.5-247	2.5	310-329	3
16.5 - 17.4	165-174	1.5	247.5-262	2.5	330-349	3.5
17.5 - 18.4	175-184	1.5	262.5-277	2.5	350-369	3.5
18.5 - 19.4	185-194	2	277.5-292	3	370-389	3.5
19.5 - 20.4	195-204	2	292.5-307	3	390-409	4
20.5 - 21.4	205-214	2	307.5-322	3	410-429	4
21.5 - 22.4	215-224	2	322.5-337	3	430-449	4.5
22.5 - 23.4	225-234	2	337.5-352	3.5	450-469	4.5
23.5 - 24.4	235-244	2.5	352.5-367	3.5	470-489	4.5
24.5 - 25.4	245-254	2.5	367.5-382	3.5	490-509	5
25.5 - 26.4	255-264	2.5	382.5-397	4	510-529	5
26.5 - 27.4	265-274	2.5	397.5-412	4	530-549	5.5
27.5 - 28.4	275-284	2.5	412.5-427	4	550-569	5.5
28.5 - 29.4	285-294	3	427.5-442	4.5	570-589	5.5
29.5 - 30.4	295-304	3	442.5-457	4.5	590-609	6
30.5 - 31.4	305-314	3	457.5-472	4.5	610-629	6

This weight-band dosing has been developed based on existing data
^
27
^ and will be validated by the nested PKPD sub-study (as has been done in several HIV trials). Children generally tolerate a wide range of azithromycin doses (5-20mg/kg); however, when given in combination with artesunate, doses of 20mg/kg more commonly resulted in vomiting (versus artemether-lumefantrine)
^
28
^. Based on Monte Carlo simulations, we expect that all dose groups should reach the population reference target (adult) AUC24h of at least 3.4 h*mg/L
^
24
^, although there are no data on absorption in severe malaria, which is characterised by impaired gut function
^
25
^, hence the need for this pilot.

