### Statistical analysis

The primary analysis for the trial will describe baseline parameters (stratified by study arm) and compare primary and secondary end points by trial arm. The primary analysis will be by intention to treat and secondary analysis will include those treated per protocol (i.e., receiving five days of azithromycin).

The co-primary outcomes are change in CRP (which will be analysed using normal linear regression adjusting for baseline, using appropriate transformations) and microbiological cure (seven day) alone and as a composite with seven-day survival (which will be analysed using logistic regression and exact tests as a binary outcome). Analysis of adverse events and re-admission will use time-to-event methods through day 90 counting in-hospital death as a competing risk. Changes in CRP and other inflammatory markers will be analysed using normal linear regression (potentially on log-transformed data), using generalised estimating equations to jointly model changes at 72 hours and day-seven. Adverse events will also be summarised by body system.

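### The post-discharge adverse-event item is worded as drug-related grade 3-4 events in an open-label dose comparison, which leaves the between-arm safety comparison open to attribution bias

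*Protocol article*

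**What the plan says.** Clinical management and monitoring sets out what a doctor documents at the clinic visits after discharge. The list covers medical history since the last visit, including re-admissions, transfusions and "grade three or four adverse events related to the antibiotic interventions including severity and likely relationship of any adverse events". Just before this, the same section says "A symptom checklist and targeted physical examination will be performed at each clinic visit post-discharge". Trial assessment schedule gives the purpose of the day 7, 28 and 90 visits as "for evaluation of morbidity and toxicity".

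On blinding, Randomisation procedure says: "Clinicians will be aware of the treatment-group dose assignments, but the laboratory tests are to be performed in a blinded manner". SAEs and interim analyses provides a designated physician to review serious events and does not say whether that physician is blind to dose. The article describes no assessor of non-serious events other than the doctor at the visit.

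Adverse events are listed under Secondary outcomes. Statistical analysis compares secondary endpoints by arm, analyses adverse events with time-to-event methods to day 90, and adds: "Adverse events will also be summarised by body system". It does not say whether these are all events or only those judged related.

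For the admission itself, the only adverse-event row in Table 2 is for serious events. The table also has rows for doctors' notes, bedside observations and the case report form. Pragmatic dosing chart notes that "when given in combination with artesunate, doses of 20mg/kg more commonly resulted in vomiting", with artemether-lumefantrine as the comparator.

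**The concern.** A causality judgement is normally an attribute attached to an event already on record. Here the wording makes it part of the definition of what goes on record. In an open-label trial of three doses, a doctor who knows that a child received 20 mg/kg may be readier to call an event drug-related than one who knows the dose was 10 mg/kg, or the reverse. If related events alone enter the comparison, this difference in judgement appears as a difference between doses, or conceals a real one. No analysis can later recover events that were never written down.

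At stake is how far the adverse-event comparison can be trusted in a trial meant to inform the dose and design of a Phase III study. Vomiting is a second, smaller matter. It is the tolerability problem the article names, and it could affect how much oral drug is absorbed, yet no scheduled item for the in-hospital days clearly covers it when it is not serious.

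**Working it through.** The article gives no adverse-event rate, attribution rate, alpha or power, so there is no figure to reproduce. The check is mainly one of reading the sections together.

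**1. Is relatedness an entry condition?** In the follow-up list, re-admissions and transfusions carry no causal qualifier, whereas the adverse-event item does. The remaining words follow *including*, and so read most naturally as details to note about the listed events. The other reading has support: noting a likely relationship for any event makes little sense if only related events are admitted. The sentence bears both readings, and the first is the more natural.

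**2. Is the judgement made with knowledge of dose?** Randomisation procedure blinds laboratory tests only. It does not mention the follow-up doctor, so that this doctor knows the dose is an inference. It is a fair one, since no blinded assessor is described.

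**3. Do the filtered data feed an arm comparison?** Yes, through Secondary outcomes and Statistical analysis. Deaths, re-admissions and serious adverse events carry no stated relatedness condition, so they are not exposed in the same way.

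**4. Where would vomiting be seen?** Azithromycin is given for five days (Treatment allocation). The article's own figure for hospital stay is a median of four to five days (Justification for azithromycin for malarial sepsis). Most doses therefore fall in hospital, outside the follow-up rule. The relevant gap is Table 2, which schedules serious events only.

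**5. Illustration of scale; all rates are assumed.**

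- Children per arm: 105 / 3 = 35.
- Recorded rate = true rate × probability of being called related.
- Take the same true rate in two arms, with 50% attributed at one dose and 70% or 90% at the other.

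| True rate, both arms | Recorded, 50% attributed | Recorded, 70% attributed | Recorded, 90% attributed |
|---|---|---|---|
| 10% | 5% | 7% | 9% |
| 20% | 10% | 14% | 18% |
| 40% | 20% | 28% | 36% |

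The recorded ratio is 0.70/0.50 = 1.4 or 0.90/0.50 = 1.8 at every true rate, while the true ratio is 1.0. At a 20% true rate the expected counts are 35 × 0.10 = 3.5 against 35 × 0.14 = 4.9 or 35 × 0.18 = 6.3 children.

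The approximate chance of a nominally significant result in the direction of the more readily attributed dose is Φ[(d − 1.96·SE0)/SE1]. Here d is the difference in recorded rates, SE0 the pooled and SE1 the unpooled standard error:

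- 10% v 14%: (0.04 − 1.96 × 0.0777)/0.0775 = −1.45, giving about 7%.
- 10% v 18%: (0.08 − 1.96 × 0.0829)/0.0824 = −1.00, giving about 16%.

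With equal attribution, the chance in that one direction is 2.5% (5% over both directions). Across true rates of 10% to 40%, the figure runs from 5% to 12% with 70% attribution and from 10% to 32% with 90%. The normal approximation is rough at such small counts, and an exact test would reject less often. The distortion of the estimate matters more than the error rate.

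**The case against.** The strongest reply is that the article does not confine follow-up recording to related grade 3-4 events. A symptom checklist with no stated grade or relatedness condition is completed at every clinic visit, the visits are meant to assess morbidity as well as toxicity, and the disputed sentence itself ends by mentioning any adverse events. A journal article also condenses, and the full protocol, the case report form or the analysis plan may record and analyse all events. Much of this stands: a reader might infer that safety recording is restricted to related events, and the text does not support that. It does not dispose of the point, because the clause as written is a recording rule, not an omission, and it can be applied as a filter.

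Three further inferences should be resisted.

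- *Mild vomiting is missed.* The checklist content is not shown, and in hospital there are doctors' notes, bedside observations and case report forms. A serious-events-only row does not prove that vomiting went unrecorded.
- *The article shows 20 mg/kg to be more emetic than 10 or 15 mg/kg.* Its statement compares with artemether-lumefantrine, not with lower azithromycin doses.
- *Tolerability decides the dose.* The only selection rule, under PKPD study, concerns exposure and response: if all doses prove to lie where response no longer rises with exposure, the lowest is taken. No tolerability criterion is stated.

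It can also be said that an all-cause analysis is impossible if unrelated events were never collected. For non-serious events outside the checklist that is correct, and it limits what can now be done.

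**Conclusion.** The point holds in a limited form. The adverse-event item for post-discharge visits is worded with relatedness as a condition of entry, in an open-label trial with no blinded assessor of non-serious events described, and it feeds a comparison between doses. That exposes the comparison to attribution bias of unknown direction and size. The 1.4-fold and 1.8-fold ratios above come wholly from assumed attribution probabilities; they show what could happen, not what did. The conclusion rests on the more natural reading of an ambiguous sentence and on the inference that follow-up doctors know the dose.

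For vomiting, the supportable statement is that the article does not clearly provide for recording non-serious episodes in hospital. Serious adverse events, re-admissions and deaths are not affected by the relatedness wording. This should be corrected, with medium confidence, because the full protocol or case report form may already resolve it.

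**What to change.** Reword the rule so that grade 3-4 events at days 7, 28 and 90 are recorded whatever their presumed cause. Keep relatedness as a separate descriptive field. Name all-cause grade 3-4 events plus serious adverse events as the between-arm safety comparison.

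Trial status reports that follow-up is complete, so rewording cannot change what was collected here. For this trial the sponsor should:

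- State what was in fact recorded at the follow-up visits, and whether non-serious vomiting was captured in hospital.
- Base the arm comparison on outcomes recorded regardless of cause: serious adverse events, re-admissions, deaths, symptom-checklist items and any grade 3-4 events entered without a relatedness condition.
- Report related-only events descriptively, stating that relatedness was attributed open-label.
- Limit tolerability conclusions to what those data support.

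The cost is a change of wording in the protocol and analysis plan and, in a future trial, slightly more recording at visits that already take place. The drawback is that more background malaria events will appear in the safety tables.

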## Introduction

*Plasmodium faliciparum* malaria remains to be a common cause of hospital admission in much of sub-Saharan Africa, and plays a substantial role in under five-year mortality
^
1
^. Strategies to control or prevent malaria (including vaccines) have so far offered limited short-term protection. Over the past decade some African countries have either documented no decline
^
2
^, an increase in hospitalisations with severe
*P. falciparum* malaria
^
3
^ or a resurgence of severe malaria following a period of sustained control. Thus, prevention strategies alone in many parts of Africa will not adequately address the burden that malaria poses on health services, particularly in countries where transmission is high. Even with the best (evidence-based) antimalarial treatment artesunate, children in the Artesunate versus Quinine in the treatment of severe falciparum malaria in African children (AQUAMAT) trial had an overall mortality of 6–8.5%
^
4
^. The trial population were selected pragmatically (defined by parasite-positivity and the admitting clinician’s desire to use parenteral rather than oral antimalarials) for generalisability of the results. However, mortality in children with severe malaria would almost certainly be substantially higher outside a Good Clinical Practice (GCP)-run trial and outside selected centres with a strong track record of research; and with more stringent clinical criteria defining severe malaria
^
5
^. Thus, there is substantial potential for clinical trials addressing the safety and efficacy of adjuvant supportive therapies to not only close existing gaps in the severe malaria treatment algorithm, but also substantially improve outcomes
^
6
^.

Children with severe malaria and bacterial co-infection, largely due to enteric Gram-negative organisms with a predominance of non-typhoidal salmonella (NTS) species, have substantially higher rates of in-hospital and post-discharge mortality
^
7
^. An estimated one third of all severe malaria deaths in African children are attributable to bacterial co-infection
^
8

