### Secondary outcomes

The secondary outcome measures are:

•  Mortality at 48-hours and longer-term survival (to day 28 and to day 90).

•  Length of hospital stay (days)

•  Re-admission to hospital by 90 days

•  Adverse events

•  The population PK of azithromycin and their relation (combined with pathogen susceptibility) with treatment outcome (PD).

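### Two stated day-90 rules mishandle known post-discharge status: children traced alive outside clinic are labelled lost, and only in-hospital death is a competing event for re-admission and adverse events

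*Protocol article*

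**What the plan says.** The protocol article asks for active tracing in two places. Trial assessment schedule: "Any patient not returning for a study visit will be traced for vital status ascertainment". Clinical management and monitoring: "Any child lost to follow-up before 90 days will be traced for vital status", with attempts by phone and "follow-up with home visits, if clinic visits are not attended".

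The same section then sets a rule expressly for the statistical analysis. A patient is lost to follow-up "if they were not seen in clinic at the day 90 visit and were not known to have died".

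Under Statistical analysis, the article says that analysis of adverse events and "re-admission will use time-to-event methods through day 90 counting in-hospital death as a competing risk". It does not say how a death outside hospital after discharge enters that analysis.

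Survival to day 28 and day 90, re-admission by 90 days and adverse events are all listed under Secondary outcomes. The Introduction says that children with severe malaria and bacterial co-infection "have substantially higher rates of in-hospital and post-discharge mortality".

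**The concern.** The first rule makes the result of tracing count in one direction only. A non-attender found dead leaves the lost category. A non-attender found alive stays in it, because the only other way out is attendance at clinic. If the label decides who contributes to day-90 survival, or when follow-up stops, then known deaths are kept and known survivors are dropped or cut short. That is informative censoring created by the definition. Whatever use is made of the label, the reported loss rate is too high.

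The second rule covers the wrong deaths for re-admission. A discharged child who later dies in hospital has normally been re-admitted already, so in-hospital death in effect means death during the index admission. The competing event that matters after discharge is death elsewhere, and the rule leaves it out. Taken literally, such a child is censored as though re-admission were still possible.

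The estimates matter beyond this trial. The Discussion says that the choice of day 7, 28 or 90 mortality as the Phase III primary outcome will be informed by this pilot, so day-90 mortality and the loss rate may serve as planning figures.

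**Working it through.** The protocol gives no day-90 mortality, attendance, post-discharge death rate or re-admission rate, so there is no planned figure to reproduce. The definitions are checked first, then their possible size under assumptions.

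**Applying the definition to non-attenders at day 90**

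| Result of tracing | Not seen in clinic? | Not known dead? | Label |
|---|---|---|---|
| Found dead | yes | no | not lost |
| Confirmed alive | yes | yes | lost |
| Not found | yes | yes | lost |

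The second and third rows get the same label although the first of them has known vital status.

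**Day-90 mortality**

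Inputs: N = 105 and 20% bacteraemia (Sample size determination); case fatality 24.1% with and 10.2% without invasive bacterial infection (review figures under Bacterial co-infection in severe malaria). Using these for day 90 is an assumption: m = 0.20 × 24.1% + 0.80 × 10.2% = 13.0%. That is 105 × 0.1298 = 13.6 deaths and 91.4 survivors. Let a be the share of survivors traced alive but not seen in clinic, assumed 10% to 20%.

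- Wrongly labelled children: 91.4 × 0.10 = 9.1 to 91.4 × 0.20 = 18.3. If vital status is known for everyone, true loss is 0%, but reported loss is 9.1/105 = 8.7% to 18.3/105 = 17.4%.
- If they are excluded: 13.6/(105 − 9.1) = 14.2%; 13.6/(105 − 18.3) = 15.7%.
- If they are censored at the day-28 visit, with proportions d1 dying before and d2 after day 28, the estimate is 1 − (1 − d1) × [1 − d2/(1 − d1 − a(1 − m))]. With 2 of the deaths after day 28 (assumed), a = 20%: 1 − 0.8893 × (1 − 2/75.1) = 13.4%. With half the deaths after day 28 (assumed), a = 10%: 1 − 0.9351 × (1 − 0.0649/0.8481) = 13.6%; a = 20%: 1 − 0.9351 × (1 − 0.0649/0.7611) = 14.5%.
- If they are censored at a day-90 contact date: 13.0%, no change.

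Over a wider assumed grid (mortality 5%, 10% or 15%; a = 5% to 20%):

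| True | Excluded | Censored at day 28, half the deaths later |
|---|---|---|
| 5% | 5.3–6.2% | 5.1–5.6% |
| 10% | 10.5–12.2% | 10.3–11.2% |
| 15% | 15.7–18.1% | 15.4–16.7% |

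The overstatement is thus about 0.1 to 3.1 percentage points when either practice is followed.

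**Re-admission**

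Assume constant hazards, with re-admission risk r when death is censored (1 − Kaplan–Meier) and post-discharge death risk q. Put l = −ln(1 − r) and k = −ln(1 − q). The cumulative incidence with death competing is l/(l + k) × [1 − (1 − r)(1 − q)].

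- r = 10%, q = 2%: 0.1054/0.1256 × 0.118 = 9.9%, overstated by 0.1 points.
- r = 10%, q = 10%: 0.5 × 0.19 = 9.5%, overstated by 0.5 points.
- r = 20%, q = 10%: 0.2231/0.3285 × 0.28 = 19.0%, overstated by 1.0 points.

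For scale, the standard error of a 15% risk (assumed) is √(0.15 × 0.85/105) = 3.5 points overall and √(0.15 × 0.85/35) = 6.0 points in an arm of 35.

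**The case against.** The strongest reply is that the first rule only attaches a label. A reader might infer that traced survivors are discarded and that day-90 mortality is therefore biased. The article does not say so: it does not state that labelled children are excluded, it specifies intention to treat, and it requires vital status to be sought. If analysts censor at the contact date, mortality is unbiased and what remains is a wrong label and an inflated loss rate. This stands, and it makes the mortality bias conditional.

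A reader might also take the Introduction to say that deaths at home are common. It makes a comparative statement about co-infected children, gives no rate and does not mention place of death. The post-discharge death rates used here are assumptions only. Likewise, nothing in the article shows that attendance or late death would differ between three doses of one drug, so a bias between arms is not supported.

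The article is silent on home deaths rather than explicit that they are censored. That is true, but it names one competing event and leaves the other out, and censoring is what the stated method then implies.

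Finally, clinic attendance has a purpose. Re-admissions and grade three or four adverse events are documented by a doctor at clinic visits, whereas tracing is described for vital status. A child known only to be alive may lack those data. This also stands: one definition of loss based on vital status alone would not serve every outcome.

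**Conclusion.** The concern holds in limited form. Both rules are stated in the article, nothing elsewhere in it corrects them, and each handles known information worse than a simple alternative would. The certain consequence is that children confirmed alive outside clinic are counted as lost. An upward bias in day-90 mortality follows only from exclusion or from censoring at the last clinic visit. The effect on re-admission is small: at most about one child in 105 under the assumed rates (0.0098 × 105 = 1.03), well inside sampling error. All rates for attendance, day-90 death, post-discharge death and re-admission are assumptions.

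Only secondary outcomes are touched. CRP change at 72 hours, seven-day microbiological cure and seven-day survival are unaffected. The correction should be made because it is cheap and the estimates may inform a later trial, not because it threatens the main results.

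**What to change.** Make the handling of follow-up specific to each outcome:

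- **Survival:** define lost to follow-up as vital status unknown at day 90 after clinic, phone and home tracing. Count children traced alive as alive to the contact date, and censor the rest when last known alive.
- **Re-admission and adverse events:** censor at the last date on which that outcome was ascertained, which may be earlier than the last date known alive. Replace in-hospital death with death from any cause, in or out of hospital, as the competing event.
- **Time origin:** keep it at randomisation. Starting the re-admission clock at discharge may look natural, but it would condition on surviving to discharge, a post-randomisation event, and would leave index-admission deaths nothing to compete with.

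The cost is a few sentences of analysis wording. No new procedure is needed, since tracing was already required, provided that contact dates and what was asked at each contact were recorded. Trial status says that follow-up is complete and the data are being analysed, so the change should be dated and reported as a clarification made at that stage.
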